## Methods

### Study design, setting and population

The Best Quit Study is a 3-arm randomized controlled trial in which quitline callers are assigned to one of three treatment groups: standard quitline (cessation treatment alone), quitline plus a weight control treatment added simultaneously, or quitline plus a weight control treatment added sequentially to the cessation program. The study will be conducted at Alere Wellbeing, which operates telephone quitlines as well as a weight management program delivered by phone, mail and web. The tobacco quitline and the weight control program are based on social cognitive theory [41], utilize similar counseling call structures and are supported by comprehensive computer-based tracking and support systems. The combined treatments aim to facilitate use of tobacco and weight control treatments to increase the proportion of smokers who achieve medium (6 months) and long-term (1 year) tobacco abstinence and to minimize weight gain.

The population will include 2550 smokers recruited from Alere Wellbeing’s commercial quitlines (employer groups and health care organizations) and participating state quitlines. Alere Wellbeing operates quitlines for 28 states and more than 800 geographically diverse employer groups and health plans and serves more than 20,000 smokers per month. Study participants will be recruited from individuals who call in to a participating quitline for cessation treatment. Individuals are eligible to participate if they are 18 years or older, smoke 10 or more cigarettes per day (cpd) and are ready to quit smoking in the next 30 days. Exclusion criteria include enrolling in the web-only program, being pregnant or planning to become pregnant within three months, having diabetes, recent or planned weight loss surgery, BMI < 18.5, having an eating disorder, inability to understand English, having no access to the internet or email, being unavailable in the next two weeks, and unwilling to participate in ten counseling calls. As this study takes place in a real-world, phone-based setting, the entire recruitment and enrollment process, including informed consent, will be handled over the phone. Interested individuals who agree to hear more about the study will be transferred to a team of trained research coaches, who will describe the study in detail, obtain informed verbal consent and collect baseline data. Eligible and consenting participants are immediately randomized by a computer generated program into one of three study arms: Standard Care (tobacco only), Simultaneous (tobacco and weight), and Sequential (tobacco followed by weight) and enrolled into the study to begin intervention. A copy of the consent form (See Additional file 1) will be mailed to study participants after enrollment, along with other study materials.

Process data will be collected using Alere Wellbeing’s automated call tracking system and stored in a secure system. Outcome data will be collected 6 and 12 months after randomization (see Fig. 1: Study Design). We will collect outcome data via surveys administered first by email, then phone, then mailed, for all participants randomized into the study and who do not withdraw consent for follow-up. Strategies to promote follow-up completion include incentives for completing surveys, $2 pre-incentives sent with mailed surveys, and an additional incentive for completing the 12-month email survey within 72 h. Telephone outcome assessors, who will receive specialized training on the study, will be blinded to the intervention assignment. All outcome survey data will be collected via a secure link to DatStat, a survey collection database.

**Fig. 1 Fig1:**
[figure not shown]
Study design

### Interventions

The intervention for all three groups includes 10 coaching calls, mailed materials, and access to one or more web-based programs plus unlimited participant initiated calls for help quitting for up to 12 months from enrollment in the quitline. Standard Care participants receive 5 quit smoking calls followed by 5 calls focused on tips for healthy living (contact control calls). Participants in the simultaneous arm receive 5 calls focused on quitting smoking integrated with the weight management content followed by 5 calls focused on tips for healthy living. Participants in the sequential arm receive 5 quit smoking calls first followed by 5 weight management calls (see Table 1: Call sequence for: Quit Smoking (Q), Weight Management (W), and Contact Control (CC) groups).

**Table 1 Tab1:** Call sequence for Quit Smoking (Q), Weight Management (W), and Contact Control (CC) calls

Week:	1	2	3	4	5	6	7	8	9	10	11	12	13	14	15
Standard care	Q1		Q2	Q3			Q4			Q5	CC1: Sunscreen	CC2: Preventing the Flu/Hand Washing	CC3: Pedestrian Safety	CC4: Disaster Preparedness	CC5: Energy Savings/Home Efficiency
Sequential	Q1		Q2	Q3			Q4			Q5	W1: Getting Started	W2: Master the Art of Eating Well	W3: Sitting Less, Moving More	W4: Stress and Weight	W5: Wt Call Wrap up
Simultaneous	Q1/W1: getting started		Q2/W2: Master the Art of Eating Well	Q3/W3: Sitting Less, Moving More			Q4/W4: Stress and Weight			Q5/W5: Wt Call Wrap Up	CC1: Sunscreen	CC2: Preventing the Flu/Hand Washing	CC3: Pedestrian Safety	CC4: Disaster Preparedness	CC5: Energy Savings/Home Efficiency

#### The smoking cessation intervention

All participants will receive standard cessation treatment services as dictated by their coverage plan, individual needs, and preferences. This includes the Quit For Life® and state quitline programs, which combines individualized telephone counseling, mailed written materials, and an interactive online program (Web Coach®) designed to complement the phone-based treatment sessions. Participants receive up to 5 counseling calls (1 reactive; 4 proactive), each designed to provide practical expert support to help participants develop problem-solving and coping skills, secure social support, and design a plan for successful cessation and long-term abstinence. As is standard in the quitline programs, participants may be eligible to receive over-the-counter (OTC) and prescription cessation medications, including Nicotine Replacement Therapy (NRT) in the form of patch, gum or lozenge, and varenicline. Because eligibility for cessation medications varies by state or commercial contract, medications may not be provided uniformly across all study participants.

#### The behavioral weight control intervention

The weight management program (Weight Talk®) is a phone and web based weight management-lifestyle program. The program integrates behavioral, psychological and biological science with highly skilled coaching. Content of the intervention comes from physical activity and dietary behavior change interventions proven to be efficacious [42–45]. For this study, Weight Talk® will act as the brief, adapted version of the weight control program used in the prior efficacy study [27]. All coaching calls, the mailed materials and the interactive web encourage and support goal setting and regular self-monitoring of weight, choice of foods, calorie reduction, physical activity, and stress reduction. The recommendations that form the basis of Weight Talk® include the NIH Clinical Guidelines on Identification, Evaluation and Treatment of Overweight and Obesity in Adults as well as the NIH-developed “Dietary Approaches to Stop Hypertension” (DASH) protocol [46]. The DASH diet has been proven to not only help reduce body weight but also to lower blood pressure, blood lipids and diabetes risk factors independent of weight control [46, 47]. The physical activity component of the program is based on the U.S. Public Health Service Guidelines (http://www.ahrq.gov/professionals/clinicians-providers/guidelines-recommendations/tobacco/index.html). The activity component encourages more moving and less sitting with an overall goal of walking 3 to 4 times per week and gradually increasing the time and speed up to > =60 min per session. The stress reduction component helps individuals identify and control stressful situations, find and practice coping skills and monitor progress. The stress reduction module uses evidence based behavioral treatments to help participants reduce the harmful effects of stress that are common in dieters as well as in smokers [48]. The treatment goal is to prevent stress from inhibiting successful behavior change. For this trial, Weight Talk® will be adapted to focus on prevention of weight gain rather than weight loss for people trying to quit smoking. A registered dietician will work with participants to set a calorie goal of approximately 300 cal fewer than their current diet. Reducing calories by this amount is likely to offset the potential weight gain associated with a reduction in metabolism associated with withdrawal of nicotine. Weight will be assessed during each counseling call and calorie adjustments can be tailored to each individual.

#### Healthy lifestyle contact control calls

The standard of care quitline program consists of 5 counseling calls. Because adding Weight Talk® to the smoking cessation treatment in the sequential treatment results in a total of 10 calls, five neutral (contact control) calls need to be added to the standard 5-call quitline group and the simultaneous weight group to equalize the number of contacts. Equality in call number reduces the potential for inequality in subject burden, differential dropout rates and differential response rates to the 6 and 12 month surveys. The ‘contact control’ calls will be delivered by trained coaching staff and the duration is approximately that of a standard care call. The contact control calls will not include weight or tobacco related content. We therefore chose the following ‘neutral’ topics, the content of which is unlikely to affect smoking or a person’s weight:Sunscreen Protection (the coach discusses risks of excessive sun exposure, and behavioral steps a person can take to protect themselves and family).Prevent the Flu/Hand Washing (the coach discusses steps a person can take to reduce their risk of contracting influenza).Pedestrian Safety (the coach provides education about pedestrian safety and tips to increase safety as a pedestrian or driver).Disaster Preparedness (the coach provides a background on the importance of disaster preparedness and provides recommendations on steps a person can take).Energy Savings/Home Efficiency (the coach discusses implications of inefficient energy consumption in homes and steps to reduce costs).

#### Counselor qualifications and training

Separate teams of equally competent counselors will deliver the tobacco or the weight based treatment. Tobacco cessation specialists (quit coaches) will be college educated with at least two years of counseling experience, consistent with prior quitline intervention trials [37, 40, 49]. Weight coaches will also be college educated and have at least two years of counseling experience. Registered dieticians who deliver the second call in the Weight Talk® program will be board certified and experienced. All counselors will have completed at least 100 h of training in the treatment approach as well as ongoing call monitoring and supervision.

### Data safety and monitoring board

The DSMB will consist of at least three independent members who, collectively, have experience in the conduct and monitoring of randomized clinical trials. A quorum will require at least two members. Upon convening, the DSMB will vote on who will serve as the chair. The DSMB membership is restricted to individuals free of apparent significant conflicts of interest. The source of these conflicts may be financial, scientific or regulatory in nature. Thus, study investigators are not members of the DSMB. DSMB members may not own stock greater than value allowed by institutional policy, in or have consulting agreements with a tobacco industry sponsor. The DSMB members will disclose conflicts of interest to fellow members. Any DSMB member who has or develops a significant conflict of interest should resign from the DSMB. DSMB membership is for the duration of the clinical trial. If any members leave the DSMB during the course of the trial, the PI will promptly appoint their replacement. The expected frequency of the DSMB meetings will be twice annually. Ad hoc meetings may be scheduled as needed. The DSMB will hold its first meeting prior to the study launch and will hold its second meeting three months after study launch. The study team will prepare open and closed reports for DSMB members to review on a quarterly basis. The open report will include the study design, protocol amendments, status of dropouts, and compliance. The closed report will be blinded to the PI and will include demographics by study arm, analyses of primary and secondary efficacy endpoints, and severe adverse events (SAEs). The purpose of the DSMB meetings is to review the conduct of the trial to date and assess safety and efficacy of the study intervention. The DSMB will review severe adverse events and determine whether the study should be prematurely discontinued.

### Discontinuing intervention

We will discontinue weight treatment for participants who report during the course of treatment a BMI < 18.5, pregnancy, or other condition that would have made them ineligible for the study at enrollment, however they may continue with the standard tobacco cessation program. There are no restrictions on concomitant care or interventions for the participants during course of the trial.

### Intervention fidelity

To monitor adherence to the cessation and weight intervention protocols (and the healthy living protocols), four raters will assess a 10 % random sample of participants’ audio-taped calls. Treatment fidelity will be assessed using a Call Quality Monitoring Tool (CMT) for the study. Treatment fidelity for Quit Coaches includes evaluation of implementing correct procedures for assessing and dosing of NRT and adherence to treatment protocols according to the PHS Guidelines [10] and recommended theory based topics advised for each call. A similarly rigorous CMT will be used to code recorded calls delivered by the Weight Coaches to assess their adherence to content specific to the weight control intervention, including their ability to utilize Social Cognitive Theory (SCT) to identify and help participants’ overcome their barriers to change [41]. Analysis of treatment fidelity will be performed quarterly. If fidelity for any sampling falls below 80 %, the pool of coaches will receive booster trainings on study content.

### Measures

Data for analyses will come from information collected when a person registers with the quitline, baseline data collected by a quit coach, 6 and 12 month phone or on-line follow-up data collected by a survey team and Alere’s tracking information on number and duration of counseling calls completed.

**Primary outcome measures** will be self-reported 30-day point prevalent abstinence and self-reported change in weight at 6 months.

**Secondary outcome measures** include 7-day point prevalence and continuous abstinence at 6 and 12 months, and reduction in amount smoked in continuing smokers. Other data will include descriptive and process data for analyses of mediators and moderators of intervention effects and cost data.

Survey content will be derived from standardized validated measures used to assess tobacco history, weight variables and outcomes, and from prior research findings and theoretical underpinnings of efficacious clinical trials [27, 33, 34, 37, 40, 50]. Most of the following measures will be assessed at baseline and/or 6 & 12 months and used to describe participants and evaluate outcomes.

*Demographics:* age, gender, race, ethnicity, education, height, weight, and other general demographics.

*Chronic Disease:* assessed by asking participants if they have ever been diagnosed with diabetes, heart disease, asthma, or a lung disease.

*Depressive symptoms:* measured with the PHQ-2, a 2 item screening measure for depressive symptoms that has demonstrated strong criterion and construct validity. The scale uses a 4-point response option to assess frequency of dysphoria and anhedonia. Sensitivity of the PHQ-2 has been reported at 84 %, with 72 % specificity for a cut score of 3 [51].

*Perceived stress:* measured with the 4-item Perceived Stress Scale (PSS), to assess the degree to which respondents find their lives to be stressful. The PSS has been shown to be a valid and reliable measure with alpha reliability coefficients from .84 to .86 [52]. PSS scores have been shown to be related to smoking relapse [53].

*Smoking/quit attempt history:* lifetime and current smoking, cigarettes smoked per day, history of quit attempts, prior use of nicotine replacement and other cessation treatments, and exposure to other household users.

*Nicotine dependence:* Fagerström Test of Nicotine Dependence (FTND) [54], which is the most commonly used measure for assessing nicotine dependence and is predictive of abstinence [55].

*Self-efficacy for quitting:* using the question “How confident are you that you could quit smoking for good?” which has been used to assess confidence and predict smoking cessation [56].

*Self-efficacy for preventing weight gain:* using the weight concerns questionnaire [57].

*Weight concerns:* assessed with 2 questions: “On a scale of 0–100, how concerned are you about gaining weight after quitting?” and “On a scale of 0–100, how concerned would you be if quitting smoking caused you to permanently gain 10 lb?”

*Physical and sedentary activities –* using standard measures to assess days per week (and minutes/day) in moderate/vigorous activity.

*Dietary behaviors:* assessed by asking about the number of fruits and vegetables consumed in a typical day and the number of days per week participants include at least 5 fruits and vegetables.

*Treatment utilization:* assessed via automated records of use of Alere Wellbeing counseling calls, the website, pharmacotherapy, and other services provided by the tobacco quitline. Utilization of treatments not provided through the study will also be assessed in the follow-up survey.

*Smoking outcomes:* assessed at 6 and 12 months to characterize 7- and 30-day point prevalence reports of nonsmoking and continuous abstinence using definitions recently recommended by the Society for Research on Nicotine and Tobacco (SRNT) [58].

*Reduction in amount smoked:* asked for those who continue to smoke at 6 months or 12 months and calculated as the difference in cigarettes smoked per day at baseline and follow-up.

*Post-cessation weight gain:* the difference between self-reported weight at registration/baseline and follow-up.

*Outcome expectations for success at smoking cessation and weight control:* single-item 10-point scales to rate participants’ expectations about the degree to which treatment would (a) help them quit smoking, (b) minimize weight gain, and (c) be effective overall. In the original efficacy trial [27], one-month test–retest reliabilities for these single-item scales ranged as follows: .36–.71 for outcome expectations about quitting smoking, .42–.59 for expectations about minimizing weight gain, and .34–.74 for expectations about the program overall, with ratings showing increased reliability later in treatment. Data from the original efficacy trial indicates that adding weight management increased outcome expectations for abstinence [27]. We will assess whether groups are similar at baseline on these measures and will evaluate these measures in mediator analyses.

### Sample size and power analysis

Alere’s historical 30+ day self-reported abstinence rate at 6 months based on an intent to treat protocol (all eligible for survey are included) is 29.6 % for employer and health plan clients and 20 % for state quitlines. The lower quit rates for state quitlines likely reflects socioeconomic differences (eg more uninsured smokers and lower education and income). Survey response rates are also lower in state quitlines. By enrolling 850 participants per treatment group, we expect to have 80 % power to detect a difference in the abstinence rate between the standard quitline control condition and the combined treatment groups of 5.7 % or greater (ie an odds ratio of 1.30) using a Fisher’s exact test. Similarly, we can detect a difference between standard care and either of the combined treatment groups of 6.5 % (OR = 1.34) or greater. The detectable odds ratio may be slightly smaller when testing for treatment effectiveness using logistic regressions controlling for baseline BMI, gender, age, and nicotine dependence. We estimate that at 12 months the abstinence rates will decrease by 3 % in each group, resulting in 80 % power to detect a change of 5.5 % (ie an odds ratio of 1.31). Effect sizes from other studies have shown that an increase in quit rates of 2.5 % or greater are clinically significant. For example, the quit rate without advice from a physician is 7.9 % versus 10.2 % with physician advice [10]. Our detectable effect size is also comparable to the effects of many different treatments that are widely applied in clinical practice. For example, without help, individuals have an estimated 10.8 % abstinence rate versus 13.1 % with proactive telephone counseling, 13.9 % with group counseling, and 16.8 % with individual counseling [10]. Since behavioral counseling is recommended, this demonstrates that increases on the order of 2.3 to 6.0 % are clinically relevant. Data from Alere’s standard services experience and a prior study were used to calculate the standard deviation of calculated post-treatment abstinence rates [37].

### Statistical analysis plan

*Aim 1.* The primary cessation and weight change outcomes will be assessed at 6 months and the secondary outcomes at 12 months. We hypothesize that combined treatments will be more effective than standard treatment and that sequential treatment will be more effective than simultaneous treatment for increasing quit rates or reducing weight gain, without harming the other outcome. The primary analysis approach for testing the effectiveness of the combined treatments on cessation will be logistic regression with an indicator for the main effect of treatment and an interaction term to account for the difference in treatment effectiveness of the two treatments. The regression equation will also include baseline characteristics that are predictive of abstinence (age, gender, etc.) and an indicator of whether the participant is qualified for receiving NRT through their State quitline plan. Analyses of cessation will be conducted three ways: 1) using multiply imputed values for missing cessation status; 2) on the set of responders to follow-up (ie, those for whom we know the cessation outcome), 3) assuming that non-responders (lost to follow-up) have relapsed. We will also conduct sensitivity analyses for missing cessation results by reanalyzing the data with different assumed probabilities of relapse. The primary analysis approach for testing the effectiveness of the combined treatments on weight will be linear regression. The regressions will include an indicator for the main effect of treatment, an interaction term to account for differences in treatment effectiveness, current cessation status and the interaction of treatment group and current cessation status as covariates, thus allowing estimates of weight gain for all participants and (as secondary analyses) for quitters and smokers. A regression approach that is robust to heterogeneity in variance will be used. We will address missing values using multiple imputation as well as conducting sensitivity analyses with different assumed amounts of weight gain for non-responders to determine how extreme such weight gains (or differential weight gains among non-responders in different groups) would need to be to invalidate statistically significant results.

For all of the aims, preliminary analyses will include summary statistics (mean, standard deviation, skewness, kurtosis, range), cross tabulations of baseline variables and outcomes for each group, correlations among variables, and plots of outcome variables versus time. Standard regression diagnostics will be performed including examination for heteroscedasticity, outliers, observations with large leverage, observations with large influence, and normality of residuals (where appropriate). Outcome variables may be transformed to improve the normality of residuals. Plots (such as residuals versus covariates and residuals versus fitted values) will be generated to examine the model fit. The Benjamini-Hochberg procedure will be used to adjust the p-value for multiple comparisons separately for primary and secondary measures. The general analysis approach for the secondary measures will be repeated measures logistic, ordinal, Poisson, or linear regression depending on the type of outcome measure [59].

*Aim 2* involves analyses to test the cost-effectiveness of the combined interventions over standard care for cessation and for weight. We hypothesize that combined treatments are more cost effective than standard treatment and sequential more cost-effective than simultaneous for cessation and weight. With respect to cost per quitter, cost-effectiveness analyses will be conducted to quantify: 1) the cost per quitter for the standard and combined treatment, 2) the incremental cost per quitter of the combined treatment (relative to the standard cessation program), and 3) the relative cost-effectiveness of the combined treatment versus other treatments in the literature. Treatment costs will be calculated on the basis of Alere’s employer and state reimbursements for the smoking cessation program (which may include NRT treatment) and weight management treatment. In addition, we will calculate the cost per quality adjusted life year gained using the approach described by Javitz [60]. With respect to weight gain, cost-effectiveness analysis will be conducted to calculate the cost per pound not gained (ie, the additional cost of the weight management treatment divided by the difference between the weight gain in the standard and combined treatment group) and this cost will be compared to medical costs associated with weight gain from the literature [61–63] and to the cost per pound lost from commercially available weight reduction programs (since presumably individuals in the standard quitline group could use such programs to lose weight or prevent weight gain).

*Aim 3* includes analyses to evaluate theoretically pre-specified mediators of treatment effects on cessation.

To test whether changes attributable to the weight management program mediate the cessation rate, we will examine changes in weight concerns, weight, outcome expectancies on quitting, and self-efficacy in quitting without weight gain. Mediation implies a causal hypothesis whereby an independent variable (ie, the weight management program) causes a mediator (eg, reduced weight concerns) that causes a change in a dependent variable (ie, cessation) [64]. We will follow four steps to test mediation effects [65, 66]. For example, to assess whether reduced weight concerns mediates cessation, we must: (1) demonstrate significantly different cessation outcomes for weight management and comparison groups, (2) demonstrate differences in weight concerns by condition, (3) establish that reduced weight concerns is significantly related to cessation rate, and (4) show that the effect of a weight management intervention on cessation rate is significantly less after controlling for change in weight concerns. We will further test whether changes in outcomes expectancies of treatment on quitting, self-efficacy in quitting without weight gain, physical activity and diet (eg fruits and vegetables) mediate the effect of the weight management program on weight gain. Regression analyses will be conducted to examine the moderating effects on cessation and weight gain of baseline characteristics of BMI, age, gender, weight concerns, nicotine dependence, outcome expectancies and self-efficacy in quitting. Moderators will be included in the regression analyses as mean-centered covariates and as interaction terms with the combined treatment group indicator.

Exploratory analyses will also assess mediators of weight gain and whether baseline BMI, weight concerns, self-efficacy, outcome expectancies, nicotine dependence, use of medications, age and gender moderate the effectiveness of the different interventions for cessation and weight outcomes.

All analyses will be conducted using SAS or STATA software.

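### The medication covariate is worded for state plans only, the weight-change model lists no baseline weight, and quitline type is named in no model: a modest coding and precision fix

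*Protocol article*

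**What the plan says.** All references are to the protocol article.

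- **Cessation model** (Statistical analysis plan, Aim 1). Besides the treatment terms, the logistic regression includes "baseline characteristics that are predictive of abstinence (age, gender, etc" and so on, an open list, plus "an indicator of whether the participant is qualified for receiving NRT through their State quitline plan". The power section mentions "logistic regressions controlling for baseline BMI, gender, age, and nicotine dependence" for the same kind of model. Neither place names quitline type.
- **Who is enrolled and who gets medication.** Study design, setting and population recruits from both commercial and state quitlines. The smoking cessation intervention states: "Because eligibility for cessation medications varies by state or commercial contract, medications may not be provided uniformly across all study participants".
- **What is known about quitline type** (Sample size and power analysis). Historical 6-month abstinence is "29.6 % for employer and health plan clients and 20 % for state quitlines", and survey response is described as lower in state quitlines, without a figure.
- **Weight model** (Statistical analysis plan). The linear regression has treatment terms together with "current cessation status and the interaction of treatment group and current cessation status as covariates". Baseline weight and BMI are not listed.
- **Weight outcome** (Measures). It is "the difference between self-reported weight at registration/baseline and follow-up". Baseline weight is among the collected items: "age, gender, race, ethnicity, education, height, weight, and other general demographics".
- **Missing data.** Multiple imputation is planned for both outcomes. The variables in the imputation models are not listed.

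**The concern.** A covariate written into the primary cessation model does not match the article's own account of how medication is made available. A commercial caller whose contract supplies medication either has no defined value or, taken literally, shares the not-eligible level with a state caller who has no NRT. That level would then mix callers from the better-quitting population with callers from the worse-quitting one, and the coefficient would not measure medication eligibility.

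The other two parts concern efficiency and missing data. A change score with no baseline term gives up some precision and leaves any chance imbalance in baseline weight unadjusted. Quitline type is the one characteristic that the article itself ties to both outcome and response. It is therefore a natural member of the imputation model, and it matters most for the absolute quit rates that feed the cost-per-quitter analysis in Aim 2.

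**Working it through.** **1. The plan's own power figures.** Inputs: 850 per group, control rate 29.6 %, 80 % power, Fisher's exact test. Alpha is not stated; two-sided 0.05 is assumed.

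- 5.7 points: OR = (0.353/0.647)/(0.296/0.704) = 1.298. Fisher power for 850 vs 1700 is 82.0 %.
- 6.5 points: OR = (0.361/0.639)/(0.296/0.704) = 1.344. Fisher power for 850 vs 850 is 80.8 %.

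Both stated odds ratios (1.30 and 1.34) are reproduced, and they correspond to the commercial rate. At 20 %, 5.7 points would be OR 1.38.

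**2. What the medication indicator would pick up if commercial callers fell in the not-eligible level and quitline type were absent.** Assumptions, none in the article: 50:50 mix, half of state callers NRT-eligible, eligibility worth d points around the 20 % state average.

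- Level 1 = 20 + d/2. Level 0 = (2 × 29.6 + 20 − d/2)/3.
- d = 4: level 1 = 22.0 %; level 0 = (59.2 + 18)/3 = 25.7 %. Eligibility looks harmful although it was assumed helpful.
- The two levels are equal when 20 + d/2 = 26.4 − d/6, that is d = 9.6. Below that the apparent sign is reversed.

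**3. Gain from adding quitline type to the cessation model.** The odds ratio between types is (0.296/0.704)/(0.20/0.80) = 1.68. The state share f is not given. Wald power for a within-type OR of 1.30, 850 vs 1700:

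| State share (assumed) | Power without type | Power with type |
|---|---|---|
| 25 % | 80.0 % | 80.3 % |
| 50 % | 77.4 % | 78.0 % |
| 75 % | 74.9 % | 75.3 % |

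Variance explained at f = 0.5: 0.25 × 0.096² / (0.248 × 0.752) = 1.2 %. A chance imbalance of 1.96 SD is 1.96 × √[0.25 × (1/850 + 1/1700)] = 4.1 points of state share. It moves the abstinence difference by 0.041 × 9.6 = 0.4 points.

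**4. Absolute quit rates if imputation ignored quitline type.** Assumptions: 50:50 mix, historical rates true, data missing at random within type, no other covariate standing in for type. The true rate is (29.6 + 20)/2 = 24.8 %. The imputed overall rate then equals the responder rate.

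| Response, commercial/state (assumed) | Responder rate | Overstatement | Cost per quitter relative to truth |
|---|---|---|---|
| 60 %/50 % | (0.6 × 29.6 + 0.5 × 20)/1.1 = 25.2 % | 0.4 points | 24.8/25.24 = 0.983 |
| 70 %/50 % | (0.7 × 29.6 + 0.5 × 20)/1.2 = 25.6 % | 0.8 points | 24.8/25.6 = 0.969 |
| 70 %/40 % | (0.7 × 29.6 + 0.4 × 20)/1.1 = 26.1 % | 1.3 points | 24.8/26.11 = 0.950 |

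Cost per quitter is cost divided by quitters, so it is understated, here by about 2–5 %.

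**5. Gain from baseline weight.** Let r be the correlation of baseline with follow-up weight (not in the article), with equal variances and cessation terms ignored. The change-score variance is 2σ²(1 − r). With baseline adjustment it is σ²(1 − r²). The ratio is (1 + r)/2. The reduction is 10 % at r = 0.8, 5 % at 0.9, 2.5 % at 0.95 and 0.5 % at 0.99.

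**The case against.** The strongest reply is that little here is an error.

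- **Open covariate list.** The rule is that predictors of abstinence enter the model, and the named examples are plainly illustrative: the power section names BMI and nicotine dependence, which the analysis section does not. A reader might infer that quitline type is excluded. The text does not support that; it is only unnamed, and a fuller plan may list it. This stands.
- **Imputation.** A reader might infer that the planned imputation is biased. The article lists no imputation variables, so step 4 is conditional. Education, a collected measure, could absorb part of the gap, which the article attributes to socioeconomic differences. The analysis that counts non-responders as relapsed does not depend on imputation. This stands too.
- **Coding of commercial callers.** No sentence assigns them to the not-eligible level. If quitline type were in the model, a state-specific NRT term could be a coherent nested term. That softens step 2 but leaves commercial eligibility unrepresented, contrary to the article's own statement that it varies by contract.
- **Validity.** A change-score analysis in a randomized trial is valid, and a poorly coded baseline covariate does not bias the treatment contrast. This stands in full. The case for baseline weight is precision only.

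**Conclusion.** The point holds as a coding and precision matter. The firmest part is textual: the medication indicator is defined through the state plan, while the article enrols commercial callers whose eligibility varies by contract. The absence of baseline weight from the listed weight model is also clear, though its value rests on a correlation that the article does not give (0.5–10 % of variance for r from 0.99 to 0.8). Quitline type is unnamed rather than excluded. Naming it gains less than 1 point of power at any of the assumed state shares, and its better use is in imputation.

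A reader might infer that the comparison between arms is biased. It is not: assignment is randomized, and eligibility follows from the caller's plan rather than from the arm. A reader might also expect overstated quit rates to raise cost per quitter; they lower it. The 0.4–1.3 point overstatement applies only if imputation ignores quitline type, and it depends on the assumed mix and response rates.

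**What to change.** 1. Redefine the indicator in the cessation model as eligibility for cessation medication under the participant's plan, whether state or commercial.
2. Add baseline weight to the weight-change regression.
3. Name quitline type (state or commercial) as a covariate in the cessation model and in the multiple-imputation models.

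These changes concern analysis coding only and leave what participants receive untouched. The cost is a few degrees of freedom among 2550 participants. Baseline weight is already a listed measure. Quitline type should follow from recruitment source. Commercial eligibility should follow from the contract, but the article does not list it as a data item, so its availability should be confirmed.
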